### Process evaluation

The ACE process evaluation plan follows the principles of the UK Medical Research Council guidance on process evaluation [29] and aims to:*Evaluate the quality and quantity of intervention delivery to inform conclusions about intervention effectiveness*To assess the quality of delivery of the ACE intervention we will:1.1. Audio-record participant-volunteer consultation meetings for a purposive sample of up to 30 pairs. Participants will be selected to achieve diversity in terms of age, biological sex and prior physical activity promotion experience. We will apply a fidelity checklist to code the data. This will include items to assess the quality and quantity of delivery of intervention processes that are part of the theory and logic model underpinning the ACE intervention. Scoring will be based on the Dreyfus scoring system for assessing clinical consultation skills [30]. Scoring will be completed by two coders independently. Encrypted digital audio recording devices will be used to record the consultations. Volunteer-participant contact time (intervention dose) will also be recorded and related to outcomes.1.2. Conduct semi-structured individual interviews with up to 30 volunteers and volunteer managers (all volunteer managers at each site) to identify variations in intervention delivery, provide feedback on the ACE training and implementation challenges. We will purposively sample volunteers to achieve diversity in age, biological sex, ethnicity and area deprivation and include volunteers who drop out of the programme.*I**nvestigate the proposed mechanisms of change, outlined in the ACE logic model and seek alternative explanations if this model is not supported*2.1. Administer brief questionnaires to participants and peer-volunteers at the baseline, 6-, 12- and 18-month data collection points (see measurement schedule, Table 1). The questionnaire data will be used to test hypotheses derived from the ACE logic model (Additional file 4: Appendix 4). This will include checking for between-group changes in the process variables listed in the model and mediation and moderation of the effects of the ACE intervention on the primary outcome, by changes in the process variables.2.2. Audio-record semi-structured interviews at 6 and 18 months with up to 30 participants, purposively selected for diversity in age, biological sex, ethnicity and functional status to identify whether the theorised mechanisms outlined in the logic model are evident in participant experiences and to identify ways in which the logic model could be refined. The data and data analysis will be integrated with that from volunteers/volunteer managers to further refine the logic model.

Analysis: The audio recordings will be transcribed verbatim and organised using the computer software NVIVO. All qualitative data will be analysed using thematic analysis, using the ACE logic model as an initial framework for coding.3.*U**nderstand the role of context and systems to inform whether and how the findings can be generalised.*We will identify systems-level and contextual barriers and facilitators of engagement with the intervention. This will inform future implementation of the intervention.3.1. Prior to the delivery of the ACE intervention, the researchers, service users and a wide range of stakeholders will co-produce a systems map [14, 31] to generate a comprehensive model, outlining the interplay between individual, systemic and contextual factors influencing physical activity and social engagement of the target population — and how this complex community-based public health intervention interacts with/affects these systems over time.This will be achieved via a series of audio-recorded half-day workshops held in each implementation site with (a) older people representing the target group who are not participating in ACE, and diverse in age, biological sex, functional ability, deprivation, ethnicity); (b) people with experience of volunteering to support older people; and (c) key active ageing agencies and organisational stakeholders (e.g. local authority service managers, VCSE organisations, public health, social care workers, activity session leaders, GPs and community nurses). The initial systems map will be used to (1) to refine the ACE intervention-delivery and recruitment strategies and (2) identify opportunities for enhanced joined action to support ACE delivery in each community.3.2. At the first stakeholder workshop, participants will be given a brief survey of relationships. This will ask them to identify the names and organisations of people who they consider important in their work in promoting physical activity with older people. This will be turned into a Social Network Analysis diagram using KUMU software [32]. This shows the extent and strength of relationships across the network and identifies key agencies or individuals who are central to the effectiveness of the network.

Both the methods above will be repeated post-intervention (with the same group of participants (the ‘map makers’) as well as with a group of up to 15 ACE participants and peer volunteers. This will identify changes and mechanisms of change in local systems and any strengthening of social networks. We will particularly seek to identify changes relating to the introduction of the ACE intervention into the community (if any). Changes in social networks will be shown through changes in key Social Network Analysis measures including degree; closeness; and betweenness measures [33].

We will seek to enhance the trustworthiness and depth of the analysis by inviting participants’ feedback on summaries of the analysed data. Our PPI group will also be involved in the interpretation of the data through workshops to discuss transcripts and the researchers’ interpretations of the data.

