**Methods/design:**

Community-dwelling, older adults aged 65 years and older (*n* = 515), at risk of mobility disability due to reduced lower limb physical functioning (Short Physical Performance Battery (SPPB) score of 4–9 inclusive) will be recruited. Participants will be randomised to receive either a minimal control intervention or ACE, a 6-month programme underpinned by behaviour change theory, whereby peer volunteers are paired with participants and offer them individually tailored support to engage them in local physical and social activities to improve lower limb mobility and increase their physical activity. Outcome data will be collected at baseline, 6, 12 and 18 months. The primary outcome analysis (difference in SPPB score at 18 months) will be undertaken blinded to group allocation. Primary comparative analyses will be on an intention-to-treat (ITT) basis with due emphasis placed on confidence intervals.

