### Sample size calculation

The ACE trial will recruit a total of 515 participants across four study sites.

Effect Size: The primary aim is to assess the long-term (18-month) effect of a peer volunteering/physical activity intervention on changes in SPPB scores. A difference of 0.5 points in the SPPB score has been defined as a minimum clinically meaningful change [8, 19].

Using baseline data from 777 adults with the same inclusion criteria as we propose for this study (from our REACT trial [20, 21]), the standard deviation for SPPB scores in this population is 1.56. This is identical to the standard deviation observed for SPPB scores in the US-based LIFE trial (SD = 1.6, *N* = 1635). To detect a difference of 0.5 points in SPPB with 90% power and 5% significance, 206 participants are required per arm. Assuming a 20% loss to follow-up at 18 months [based on a 19% loss to follow-up at 24 months in our REACT study], the total sample size required is 515.

We will recruit a minimum of 130 volunteers (aged 55 + years) to support two intervention participants each. Since the cluster sizes in the intervention arm are minimal (less than two participants to each volunteer on average) we will not inflate the sample size required for clustering at the level of volunteer. However, the analytic strategy will present results from a partial cluster model to assess the small amount of possible clustering in the intervention arm only.

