### Statistical analysis

Primary outcome analysis will be undertaken blinded to group allocation and will be on an intention-to-treat (ITT) basis with due emphasis placed on confidence intervals. Using appropriate descriptive statistics we will assess any imbalance between the trial arms at baseline and describe the characteristics of participants. The primary analytic strategy will employ a linear mixed model including baseline, 6- and 18-month SPPB outcome time points as well as the randomisation stratification variable (site). Treatment and time variables together with a categorical treatment by time interaction will be fitted to explore treatment effects over time. All results will be presented with 95% confidence intervals and *p*-values. A partial cluster regression model to account for the possible clustering effects of participants within volunteers will also be fitted to the primary outcome within the mixed model framework. Intra-cluster coefficients will be estimated and reported if non-negligible.

Depending on the extent of missing primary outcome data, the primary analysis will be repeated using the complete data set generated using multiple imputations. Sensitivity analyses will be conducted to investigate the potential effects of non-random missing data and of any co-interventions on the results and conclusions.

Secondary outcome analysis will be undertaken using the same general approach as for the primary analysis, using the baseline, 6-, 12- and 18-month follow-up data. This will include linear or generalised linear mixed regression models for continuous or binary outcomes as appropriate.

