#### Sub-group analyses

Subgroup analyses are not powered for in this trial analysis but will be included and interpreted as exploratory only. Key pre-specified moderators of interest are area deprivation and ethnicity. If numbers allow, a group moderator interaction term will be added to the primary analysis model to investigate included moderator effects on treatment effectiveness. Other moderators to be considered for exploratory analysis include age group, sex, fall risk category and level of education.

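### The process evaluation names changes in process variables, which are measured after randomisation, as moderators of the ACE effect on SPPB; moderation should use their baseline values

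*Protocol article*

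**What the plan says.** The second aim of the process evaluation is to examine whether ACE works through the mechanisms in its logic model. Item 2.1 sets out the quantitative part. The data source is: "Administer brief questionnaires to participants and peer-volunteers at the baseline, 6-, 12- and 18-month data collection points". The analysis has two parts. The first is: "This will include checking for between-group changes in the process variables listed in the model". The second is a test of "mediation and moderation of the effects of the ACE intervention on the primary outcome, by changes in the process variables". The detailed hypotheses are referred to an additional file that is not shown.

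The outcome in question is SPPB at 18 months. The abstract gives it as: "The primary outcome analysis (difference in SPPB score at 18 months) will be undertaken blinded to group allocation".

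Moderation also appears under Sub-group analyses: "Key pre-specified moderators of interest are area deprivation and ethnicity". That section adds age group, sex, fall risk category and level of education as further candidates, and treats all of these analyses as exploratory.

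**The concern.** Randomisation protects a treatment-by-moderator interaction when the moderator is fixed before allocation, because within each level of the moderator the arms remain comparable. A change from baseline in a process variable is not fixed before allocation. Item 2.1 itself looks for an effect of ACE on these changes, so they are treated as possible consequences of treatment.

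Participants whose process variable improved under ACE need not resemble those in whom it improved under control. In an individually tailored programme, participants with better prospects may gain more from the support, with no matching pattern among controls. SPPB would then rise with process change more steeply in the ACE arm, even if ACE raised everyone's SPPB by the same amount, and the interaction test would read this as effect modification.

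What is at stake is the conclusion about the logic model. A finding that ACE works only in people whose process variable improved could be produced by selection alone, and could then shape who is offered the programme or how it is delivered.

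**Working it through.** **1. The design figure.** The protocol states: "To detect a difference of 0.5 points in SPPB with 90% power and 5% significance, 206 participants are required per arm". With SD 1.56 and a two-sided 5% test, the normal approximation is n = 2 × (1.96 + 1.2816)² × 1.56² / 0.5² = 204.6, so 205 per arm. Power based on the t distribution is 0.8993 at 205 and 0.9006 at 206, which gives the stated 206. Then 2 × 206 / 0.8 = 515. The design figure reproduces and is not in dispute. It supplies n, SD and effect for the illustration.

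**2. The wording.** In item 2.1, one closing phrase (by changes in the process variables) follows both mediation and moderation. Read plainly, change is the moderator as well as the mediator. The questionnaires run at baseline, 6, 12 and 18 months, so every change score contains a follow-up value. The moderators under Sub-group analyses are background characteristics in a separate analysis, and they do not alter what item 2.1 says.

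**3. Illustration.** Inputs from the protocol: 206 per arm, SD 1.56, effect 0.5. Assumptions, none from the protocol:
- a prognostic factor U with correlation ρ with SPPB;
- the same treatment effect for everyone, so no true moderation;
- process change M with residual SD 1 and mean 0.5 higher in the ACE arm;
- M depends on U with coefficient g in the ACE arm only.

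The model is SPPB on arm, M and arm × M. The expected false interaction is the slope of SPPB on M in the ACE arm, since the control slope is zero:

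slope = g × ρ × 1.56 / (1 + g²)

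SE = 1.56 × √{[1 − g²ρ²/(1 + g²)] / [206 × (1 + g²)] + 1/206}

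Example, ρ = 0.5 and g = 0.3:
- slope = 0.234 / 1.09 = 0.215
- SE = 1.56 × √(0.00436 + 0.00485) = 0.150
- z = 1.43
- rejection rate = Φ(1.43 − 1.96) + Φ(−1.43 − 1.96) ≈ 30%

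| ρ | g | false slope | SE | formula | simulated (3,000 trials) |
|---|---|---|---|---|---|
| 0.2 | 0.3 | 0.086 | 0.150 | 9% | 9% |
| 0.2 | 0.5 | 0.125 | 0.146 | 14% | 14% |
| 0.3 | 0.3 | 0.129 | 0.150 | 14% | 13% |
| 0.3 | 0.5 | 0.187 | 0.145 | 25% | 27% |
| 0.5 | 0.3 | 0.215 | 0.150 | 30% | 31% |
| 0.5 | 0.5 | 0.312 | 0.144 | 58% | 59% |
| 0.5 | 0.6 | 0.344 | 0.141 | 68% | 68% |

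**4. Comparison cases.** With M measured at baseline, the false-positive rate is about 5%. With M a post-randomisation change that depends on U equally in both arms, so that allocation only shifts it, the rate is also about 5%.

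**5. A stronger case.** Let M have unit variance and correlate 0.6 with U in the ACE arm only, with ρ = 0.6. The false slope is 0.6 × 0.6 × 1.56 = 0.56 points per SD. The SE is 1.56 × √[(1 − 0.1296)/206 + 1/206] = 0.149, so z = 3.8 and the false-positive rate is about 97%. The 10% to 70% range is therefore not an upper limit; it describes moderate correlations.

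**The case against.** **The wording is compressed and no interaction model is specified.** One phrase serves two nouns, and the authors may have meant it only for mediation. That is possible, and it is a reason to ask for a sentence rather than a redesign. It does not remove the point, because the article names a moderator and the one it names is post-randomisation. This is something stated, not a detail left to the analysis plan.

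**An arm-by-mediator term is a standard part of counterfactual mediation analysis.** This is correct. Fitting the term is not the error; reading it as effect modification would be.

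**The inflation depends on assumptions.** This stands too. A reader might infer that the planned analysis will give spurious moderation. The calculations support only that it can: the rate stays near 5% when change relates to prognosis equally in both arms, and it is only 9% to 14% at ρ = 0.2 with g of 0.3 to 0.5. Adjusting for baseline SPPB would also remove part of the link, so ρ is best read as what remains after adjustment.

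**The main effect of arm.** A reader might also infer that the treatment effect itself is distorted in such a model. At ρ = 0.5, the arm coefficient is 0.5 − 0.5 × 0.215 = 0.39 for g = 0.3 and 0.5 − 0.5 × 0.312 = 0.34 for g = 0.5. These are effects at zero change. At the pooled mean change of 0.25 they are 0.45 and 0.42, and at the ACE-arm mean they are 0.50. The figure depends on centring, which the protocol does not state, so it is not used as a measure of harm.

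**Mediator timing.** A reader might infer a second error: that 18-month process change will be used to mediate 18-month SPPB, where better function could be driving the change. The article does not say this. It names no mediator wave, and the 6- and 12-month waves precede the outcome. The choice of wave, the adjustment set and any sensitivity analysis for confounding are commonly left to the full protocol or analysis plan, so their absence here is not a finding.

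**Conclusion.** The point holds for moderation only. As written, item 2.1 tests moderation by variables measured after randomisation that ACE is expected to change, so the interaction is not protected by randomisation. With 206 per arm and a constant true effect of 0.5, the false-positive rate is about 5% for a baseline moderator or for a change related to prognosis equally in both arms. It is roughly 10% to 70% if change tracks prognosis only in the ACE arm, and higher still under stronger correlations. Those figures rest on assumed correlations and an assumed linear model; nothing in the protocol shows which case would apply.

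The consequence is limited to the process evaluation. The primary analysis does not use process variables: "The primary analytic strategy will employ a linear mixed model including baseline, 6- and 18-month SPPB outcome time points", with site, treatment, time and their interaction. The sample size is also untouched. The interviews with participants give a second line of evidence on mechanisms, so the logic model would not be judged on this regression alone.

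**What to change.** Replace the closing phrase of item 2.1 with a statement that moderation of the ACE effect on 18-month SPPB is tested with the baseline values of the process variables, and that changes in those variables are used only as mediators. It would help to add that the mediators are the changes from baseline to 6 and 12 months, since these come before the outcome. If an arm-by-mediator term is fitted within the mediation analysis, say that it is not interpreted as effect modification.

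The cost is one sentence, with no new data, because the baseline, 6- and 12-month questionnaires are already scheduled. If the optional clarification is adopted, process changes after 12 months would not contribute to the mediation analysis.

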### Oversight and monitoring

The ACE trial will be overseen and monitored by a Trial Steering Committee (TSC), Data Monitoring and Ethics Committee (DMEC) and a Trial Management Group (TMG).

#### Trial Steering Committee (TSC)

The TSC will consist of an independent Chair with expertise in ageing and public health; the CI; at least one Advisory Group representative, an independent medical advisor, an independent statistician, an expert in health economics, a research expert from UKActive, plus two independent academics experienced in the design, delivery and evaluation of health promoting interventions in primary care and in the community. PIs at each site and health economist may be called on to attend as needed. The TSC will meet every 6–9 months from the start of the trial, providing overall supervision of the trial, monitoring trial progress and advising on scientific credibility. The TSC will consider and act, as appropriate, upon the recommendations of the Data Monitoring and Ethics Committee (DMEC) and will have the responsibility for deciding whether the trial needs to be stopped on grounds of safety or efficacy. The TSC will be blinded to all information regarding treatment assignments until the database is locked for final analysis or if the DMEC recommends that results need to be reviewed.

#### Data Monitoring and Ethics Committee (DMEC)

A fully independent DMEC will report to the TSC. This will comprise of an independent chair plus two senior academics including a statistician. The CI, PIs and Senior trial statistician may be invited to attend to provide specific input by the DMEC Chair with the CI and statistician usually expected to attend the ‘open session’ section of the meetings. The DMEC will be responsible for the interests of the participants and its main role will be to make recommendations to the TSC as to whether the trial needs to be stopped for any ethical or safety reason (based on review of accumulating safety data). The DMEC will undertake safety data reviews every 12 months after recruitment begins, unless otherwise deemed necessary. This will include data on any adverse advents reported during the trial.

The DMEC will be responsible for identifying any need for unblinding. The DMEC will also periodically review unblinded overall safety data to determine patterns and trends of events, or to identify safety issues, which would not be apparent on an individual case basis.

Analysed data will be blinded, unless the DMEC identifies a specific need for unblinding. The DMEC will meet shortly before the TSC and will provide a report for review during the TSC meeting.

#### Trial Management Group

The TMG will consist of the CI, all co-applicants, the trial manager, two people from our Advisory Group and the researchers at each trial centre. It will meet 4 times per year to ensure accurate implementation of the study protocol and the successful conduct and completion of the study.

Following the INVOLVE guidelines (involve.org.uk), we will have Advisory Group representatives on our Trial Management Group and Trial Steering Committee.

### Safety

The Trial Steering Committee and the Data Monitoring and Ethics Committee will oversee all patient safety issues, which the ACE independent medical advisor, will review in detail. All serious adverse events (SAE) will be examined by an independent medical advisor to see if they are related to the study intervention or measurement procedures. The ethics committee, the sponsor and the Trial Steering Committee or DMEC will be notified promptly (within 24 h) of all related serious adverse events.

Any adverse event or adverse reaction will be regarded as serious if it results in death; is life-threatening; requires non-elective hospitalisation, prolongation of existing hospitalisation or elective hospitalisation that may be related to taking part in the study; results in persistent or significant disability or incapacity. Only SAEs related to the study will be reported. The CI will maintain a register of all reported serious adverse events.

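### The related-only SAE reporting rule does not fit the DMEC's duty to look for patterns across all safety data, and the two sections need reconciling

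*Protocol article*

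**What the plan says.** The Safety section of the protocol article sets out this sequence:

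- Oversight is broad: "The Trial Steering Committee and the Data Monitoring and Ethics Committee will oversee all patient safety issues".
- Ascertainment is complete: "All serious adverse events (SAE) will be examined by an independent medical advisor to see if they are related to the study intervention" or to measurement procedures.
- The ethics committee, the sponsor and the TSC or DMEC "will be notified promptly (within 24 h) of all related serious adverse events".
- Next comes the definition of a serious event, followed by an unqualified sentence: "Only SAEs related to the study will be reported".
- The register uses the same word: "The CI will maintain a register of all reported serious adverse events".

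The section on the Data Monitoring and Ethics Committee describes yearly safety reviews that include adverse events reported during the trial. It then says: "The DMEC will also periodically review unblinded overall safety data to determine patterns and trends of events", or to identify problems that case-by-case assessment would miss. The next paragraph adds: "Analysed data will be blinded, unless the DMEC identifies a specific need for unblinding".

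**The concern.** A review for patterns and trends compares counts of all events between arms, because no single event needs to look attributable for an excess to exist. A filter that keeps only events already attributed one by one removes most of what such a review compares. If the Safety section is followed to the letter, the register holds related SAEs only, and the DMEC's periodic review may rest on that register.

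The filter may also act unevenly. Relatedness is judged against the intervention and the measurement procedures. Both arms share the assessments. The ACE arm adds six months of supported community activity, while the control arm is invited to two group sessions without physical activity content. The article does not say whether the medical advisor is blinded; it mentions blinding for the main outcome assessors.

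The population is older people with limited lower-limb function. A programme that gets them out and active could raise or lower the number of admissions, fractures or deaths. An all-SAE table by arm is the direct way to see this.

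**Working it through.** **1. The two sections side by side**

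| Question | Safety section | DMEC section |
|---|---|---|
| Which SAEs are examined? | All, by the medical advisor | – |
| Which SAEs are reported? | Related ones only | Review includes adverse events *reported* in the trial |
| Which SAEs are registered? | The *reported* ones | – |
| What is reviewed for patterns? | – | Overall safety data, unblinded |

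The word *reported* links the three places. If it means the same in each, the DMEC's data reduce to related SAEs, and the review of overall data cannot be done from them. If it means onward notification in the Safety section only, the two sections agree, but the article does not say so. The 24-hour rule for related SAEs already stands earlier in the Safety section, so on that second reading the later sentence adds almost nothing.

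**2. Illustration of what the filter could do**

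The article gives no SAE rate, no relatedness share and no safety threshold, so there is no stated figure to reproduce. From the article: 515 participants allocated 1:1, so 515/2 is about 257 per arm. Everything else is assumed and shown over a range.

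*(a) Precision with all SAEs counted, equal risk p in both arms.* Let x = 257p be the number with an SAE per arm. Then SE(log RR) = √[2(1/x − 1/257)], and the 95% limits around a ratio of 1 are exp(±1.96 × SE).

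| p | x | SE | 95% limits |
|---|---|---|---|
| 10% | 25.7 | 0.265 | 0.60 to 1.68 |
| 20% | 51.4 | 0.176 | 0.71 to 1.41 |
| 30% | 77.1 | 0.135 | 0.77 to 1.30 |

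*(b) Related-only counts when the true risk is equal.* Expected count = 257 × p × r, where r is the share of SAEs judged related.

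| p | r = 10% | r = 5% | r = 1% | r = 0 |
|---|---|---|---|---|
| 10% | 2.57 | 1.29 | 0.26 | 0 |
| 20% | 5.14 | 2.57 | 0.51 | 0 |
| 30% | 7.71 | 3.86 | 0.77 | 0 |

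If r is 5–10% in the ACE arm and 1% in control, the ratio of counts is 5 to 10 with no true difference. If r is 0 in control, no ratio can be formed. If r is 5% in both arms, the ratio is 1.0 and there is no bias.

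*(c) Power to see a true excess, with the same r in both arms.* Power = Φ[(d − 1.96·se₀)/se₁], where d is the risk difference, p̄ is the mean of the two risks, se₀ = √[2p̄(1 − p̄)/257] and se₁ = √{[p₁(1 − p₁) + p₂(1 − p₂)]/257}. For 20% against 30%: se₀ = 0.0382, se₁ = 0.0379, and (0.10 − 0.0749)/0.0379 = 0.66, so power is 0.75. With r = 5% the risks become 1.0% and 1.5%: se₀ = se₁ = 0.0098, and (0.005 − 0.0192)/0.0098 = −1.45, so power is 0.07.

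| True risks | All SAEs | r = 5% | r = 10% |
|---|---|---|---|
| 10% v 20% | 89% | 10% | 15% |
| 20% v 30% | 75% | 7% | 11% |
| 20% v 35% | 97% | 11% | 18% |

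The normal approximation is rough at the small filtered counts, so those columns show only the order of magnitude. This loss arises even when relatedness is judged identically in the two arms.

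**The case against.** The strongest reply is that the Safety sentence concerns onward reporting to the ethics committee and the sponsor. Every SAE reaches the medical advisor, the DMEC is to see overall safety data, and nothing says that unrelated SAEs are kept from it. The article also condenses a full protocol, which may settle the routing.

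Much of this stands. A reader might infer that the DMEC is unable to do its review. The documents do not support that: the events are examined centrally, and no passage withholds them. What does not stand is that the wording is merely brief. The rule is stated without limit, the 24-hour rule is already given separately, and the register repeats the same word.

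A reader might also infer that the safety comparison is biased by arm. That is not established. No comparison of related SAEs by arm is stated, measurement procedures apply to both arms, and equal relatedness shares would leave the ratio unbiased.

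Nor would the trial be blind to harm. Falls and use of health and social care are secondary comparisons between arms, whatever the relatedness. They do not replace an SAE table: deaths and fractures are not named among them, and they are not stated to be DMEC input.

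Finally, the two DMEC sentences on blinding can be read together, one covering safety review and the other analysed data in general. They do not necessarily conflict, but the article leaves open whether the unblinded review is routine or needs a trigger.

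**Conclusion.** The point holds as a conflict between two stated rules, and it is worth correcting. Read literally, the related-only rule and the register built on it do not assure the DMEC the all-SAE data by arm that its pattern review needs. A difference between arms in related-only counts is plausible, given the unequal exposure, but it remains an inference.

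The size is not known from the documents. Under the assumed rates, counting only 5–10% of SAEs reduces power for the excesses examined from 75–97% to about 7–18%. Even an all-SAE table would leave moderate differences unresolved, with limits of 0.60 to 1.68 at a 10% risk and 0.77 to 1.30 at 30%. The planned sample size and the primary analysis are unaffected.

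**What to change.** 1. In the Safety section, limit the related-only rule to expedited (24-hour) notification.
2. State that the register records all SAEs in both arms regardless of relatedness, with the advisor's judgement as one field.
3. In the DMEC section, state that all SAEs are tabulated by arm for each periodic review, and that the same table appears in the final report.
4. Add that the sentence on blinded analysed data does not restrict the DMEC's periodic unblinded safety review.

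The cost is small. The medical advisor already examines every SAE, so the change means a fuller register and one table per DMEC report. The 24-hour procedure stays as it is.
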